### Data collection and management

The research team will undertake the tasks of data collection and management. Data collection will involve the use of both electronic medical records and case report forms (CRFs). Electronic health records will extract participant demographic details and relevant medical history. Additionally, researchers will systematically accumulate precise individualized data through a meticulously crafted CRF.

Following data collection, designated staff will thoroughly review the CRFs to verify the information. Once finalized, the CRFs will be secured by the head of the research site for safekeeping. After the follow-up period, the original data will be digitized, and the initial CRFs will be sealed and preserved until the designated time for unsealing.

### The trial quality control

The following rules apply to trial quality control.(1) Each center is required to designate an officer responsible for seamless coordination throughout the entire process.(2) Participant Protection and Informed Consent;(3) Strict adherence to the research protocol is imperative throughout the trial;(4) Ensure Clinical Data Integrity;(5) Timely Report of Adverse Events.

### Statistical analysis

#### Software and general principles

Data statistical analysis will be conducted using SPSS or SAS software. All analyses will adhere to the intention-to-treat (ITT) principle, encompassing all randomly assigned patients. For participants who withdraw from the trial, their data will be handled using the last observation carried forward (LOCF) method when appropriate.

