### Study design

This study is a multicenter, randomized, and controlled clinical study comparing the efficacy and safety of BJOEI combined with BSC versus BSC in patients who are refractory to all available therapy. Eligible patients will be randomized in a 1:1 ratio to either the experimental group or the control group. Both groups will receive BSC in line with the NCCN palliative treatment guidelines (Dans et al., 2021). Participants assigned to the experimental group will be administered 30 mL of intravenous BJOEI daily for 1–14 days in each 28-day cycle. Conversely, the control group will receive only BSC. Treatment for eligible patients will continue until disease progression as defined by the Response Evaluation Criteria in Solid Tumors 1.1 (RECIST 1.1) (Eisenhauer et al., 2009), the onset of unacceptable toxicity, completion of 12 months from randomization, or withdrawal of informed consent. Follow-up evaluations will occur every 2 months until either death, loss of follow-up, or the 12-month mark from randomization. The trial has been registered on the Clinical Trials research platform (ClinicalTrials.gov, ID NCT05897749), and the participant timeline and trial flowchart are displayed in Figures 1, 2, respectively.

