#### Secondary outcomes

(1) Objective Response Rate (ORR): ORR represents the percentage of patients achieving a predefined reduction in tumor volume and maintaining this reduction for a specified minimum duration, assessed in accordance with RECIST 1.1 criteria.(2) OS: OS is the interval from randomization to death caused by any factor.(3) Quality of Life Assessment: The European Organization for Research and Treatment of Cancer Quality of Life Questionnaire-Core 30 (European Organisation for Research and Treatment of Cancer, 2001) and the Anderson Symptom Assessment Scale (Giesinger et al., 2021) will be employed to assess score changes.

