#### Sample size

Many patients experience rapid disease progression with third- and fourth-line therapies, leaving them with limited therapeutic options. BJOEI has shown potential benefits for these patients.As an external pilot RCT, this study is not powered to test efficacy. A total of 60 participants (30 per arm) was selected to provide adequate precision for estimates of median PFS and variance while remaining logistically feasible. This aligns with published recommendations (15–25 per arm) and will inform the definitive phase III sample-size calculation (Sim and Lewis, 2012; Whitehead et al., 2016).

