#### Statistical description and analysis methods

For continuous variables, normality will be assessed using the Shapiro-Wilk test or Kolmogorov-Smirnov test. If normally distributed, data will be presented as mean ± standard deviation, and between-group comparisons will be performed using independent sample t-tests. If not normally distributed, data will be presented as median and interquartile range (IQR), and the Mann-Whitney U test will be applied for between-group comparisons.

For categorical variables, descriptive statistics will be presented as frequencies and percentages. Between-group comparisons will be performed using the chi-squared test or Fisher’s exact test when the expected frequency in any cell is less than 5.

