#### Time-to-event analysis

Kaplan-Meier curves will be used to estimate survival functions for overall survival (OS) and progression-free survival (PFS). The log-rank test will be employed to compare survival curves between treatment groups. Cox proportional-hazards models will be applied to calculate hazard ratios (HRs) with corresponding 95% confidence intervals (CIs), adjusting for pre-specified prognostic factors including ECOG performance status, number of prior treatment lines, and presence of liver metastases. Patients will be censored at the date of last contact for survival analyses and at the date of last tumor assessment for progression-free survival analyses.

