## Discussion

CRC stand as a significant global health burden, ranking as the third most prevalent malignancy. Substantial evidence indicates that 90% of CRC cases are diagnosed in individuals aged 50 and above. Alarmingly, the incidence of CRC among younger populations is increasing (Penz et al., 2023). The 5-year survival rate for mCRC remains dishearteningly low at 6% (Coco et al., 2012). The most effective treatment for mCRC is 5-FU-based regimens. However, disease progression after two lines of doublet chemotherapy remains inevitable. Although several drugs are the standard third-line treatment of mCRC in guidelines (Grothey et al., 2013; Dasari et al., 2023; Mayer et al., 2015), they yield minimal response rate and short PFS and OS. In general, the efficacy of third-line and subsequent treatments is unsatisfactory. Few treatment options exist for this population of patients. Traditional Chinese Medicine (TCM) theories and treatment approaches are gaining global acceptance, with integrative Chinese and Western medicine emerging as a novel avenue in cancer therapy. TCM demonstrates unique advantages in tumor treatment. BJOEI have been widely used for the treatment of cancer in China. Numerous clinical studies have shown that BJOEI when combined with FOLFOX/FOLFIRI regimens, enhances tumor treatment efficacy, improves patients' quality of life, and mitigates adverse reactions (Gao and Zhang, 2023).

In prior studies of BJOEI on CRC, the primary endpoint was the ORR. However, this measure alone cannot fully capture the clinical benefits of the trial drug. PFS is utilized both as a surrogate end-point for OS and as a primary trial end-point in itself (Robinson et al., 2014). Therefore, we hope to further objectively evaluate the clinical effectiveness of BJOEI combined with BSC from the PFS status. In addition, Safety assessments will include the incidence, nature, and severity of adverse events; serious adverse events and laboratory abnormalities. Laboratory safety assessments will include the regular monitoring of hematology and blood chemistry.

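### LOCF "their data will be handled using the last observation carried forward (LOCF) method when appropriate" is an undefined rule that falls on the quality-of-life and symptom scores and can bias their comparison, mainly if withdrawal differs by arm

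*Protocol article*

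**What the plan says.** All references are to the protocol article.

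- **Software and general principles:** of those who withdraw, it says that "their data will be handled using the last observation carried forward (LOCF) method when appropriate". This is the only missing-data rule for withdrawn participants. It names no outcome and does not define when LOCF is appropriate.
- **Secondary outcomes:** the QLQ-C30 and the Anderson symptom scale "will be employed to assess score changes".
- **Statistical description and analysis methods:** for normally distributed continuous variables, "between-group comparisons will be performed using independent sample t-tests"; otherwise the Mann-Whitney U test. No repeated-measures model is described.
- **Time-to-event analysis:** "Patients will be censored at the date of last contact for survival analyses", and PFS is censored at the last tumor assessment.
- **Study design:** "Follow-up evaluations will occur every 2 months until either death, loss of follow-up, or the 12-month mark from randomization". Progression ends treatment but not follow-up. The text gives no separate schedule for the questionnaires, and the participant timeline is a figure that is not shown.

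**The concern.** PFS and OS are censored, so LOCF has no work to do there. By elimination it acts on the two questionnaire outcomes. It assumes that a patient's score stays where it was on the day of leaving.

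That assumption is hard to defend here. Patients are refractory to all available therapy. The Sample size section says "Many patients experience rapid disease progression with third- and fourth-line therapies", and the Discussion says of standard third-line drugs that "they yield minimal response rate and short PFS and OS". If scores fall over time, a patient who leaves early is recorded as better than he or she would have been. The arm that keeps its patients longer records more of their decline and looks worse. The trial is open label with no active control, so a different rate of leaving in the two arms is plausible.

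The undefined qualifier adds a second weakness: whether and where to impute can be decided after the data are seen, in a trial where treatment is known. The pilot exists to supply parameters for a phase III trial, so a distorted quality-of-life difference could carry into its planning.

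**Working it through.** The plan states no quality-of-life figure to reproduce, so the check asks what LOCF returns when the truth is known.

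**From the documents:** evaluations every 2 months; change scores compared between arms; LOCF for withdrawals.

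**Assumed:**
- Scores are oriented so that higher is better, and fall linearly.
- The analysis is at month 6, with scores at 0, 2, 4 and 6 months.
- Time to withdrawal is exponential and unrelated to the patient's own slope.
- A patient with only a baseline score counts as zero change.
- The truth is the month-6 difference if nobody withdrew.

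**Formula.** With S(t) the share still giving scores at month t, the mean month of the last score is L = 2 × [S(2) + S(4) + S(6)]. The LOCF mean change is slope × L. If a fraction w has withdrawn by month 6, S(t) = (1 - w)^(t/6). If median retention is m months, S(t) = 2^(-t/m).

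**Values of L**
- w = 10%: 2 × (0.9655 + 0.9322 + 0.9000) = 5.595
- w = 20%: 2 × (0.9283 + 0.8618 + 0.8000) = 5.180
- w = 30%: 2 × (0.8879 + 0.7884 + 0.7000) = 4.753
- m = 2: 2 × (0.500 + 0.250 + 0.125) = 1.750
- m = 3: 2 × (0.630 + 0.397 + 0.250) = 2.554
- m = 4: 2 × (0.707 + 0.500 + 0.354) = 3.121

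**Only true withdrawals carried forward (BJOEI minus control)**

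| Monthly decline, BJOEI / control | Withdrawn by month 6, BJOEI / control | Truth | LOCF |
|---|---|---|---|
| 5 / 5 | 10% / 30% | 0 | -5 × (5.595 - 4.753) = -4.2 |
| 5 / 5 | 30% / 10% | 0 | +4.2 |
| 3 / 5 | 10% / 10% | +12 | 2 × 5.595 = +11.2 |
| 3 / 5 | 20% / 20% | +12 | 2 × 5.180 = +10.4 |
| 3 / 5 | 10% / 30% | +12 | -3 × 5.595 + 5 × 4.753 = +7.0 |
| 3 / 5 | 30% / 10% | +12 | -3 × 4.753 + 5 × 5.595 = +13.7 |

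Low, equal withdrawal costs little. Unequal withdrawal moves the estimate by several points in either direction, depending on which arm loses more patients.

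**Every early loss of questionnaires treated as a withdrawal, decline 3 / 5, truth +12**
- Median retention 3 months in both arms: 2 × 2.554 = +5.1
- 4 months BJOEI, 2 months control: -3 × 3.121 + 5 × 1.750 = -0.6

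**Sensitivity to the baseline-only assumption.** If patients with no post-baseline score are left out, L is divided by S(2).
- 10% / 30%: L = 5.595/0.9655 = 5.795 and 4.753/0.8879 = 5.353. Identical decline gives -5 × (5.795 - 5.353) = -2.2; a true +12 gives -3 × 5.795 + 5 × 5.353 = +9.4.
- 4 vs 2 months: L = 3.121/0.7071 = 4.414 and 1.750/0.5 = 3.500, giving -3 × 4.414 + 5 × 3.500 = +4.3.

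The bias roughly halves in the first case. The reversal disappears in the second, though most of the true +12 is still lost.

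**The case against.** The strongest reply is that the rule is narrow. It covers participants who withdraw. Progression and death are not withdrawal, and evaluations continue after progression. If few patients truly withdraw and the arms lose similar numbers, LOCF changes little: +11.2 or +10.4 against a true +12. The qualifier also means the trial is not bound to LOCF for every score. Quality of life is a secondary outcome in a pilot that claims no power, and much of the modelling detail would normally sit in an analysis plan that is not shown.

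Most of this stands as a limit on size. It does not remove the point. The protocol names a specific method, so this is not detail left to a later document. Even on the narrow reading, unequal withdrawal creates a false difference of about 4 points. A qualifier with no criterion leaves the choice open without improving it.

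Three stronger readings may tempt a reader, and the documents do not support them.

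- **That scores will be frozen at baseline or month 2 for most patients.** No withdrawal rate, median PFS or OS, or questionnaire schedule is given. The share whose last score is baseline or month 2 runs from 21% to 75% as assumed median time to withdrawal goes from 12 months to 2. Nor does the protocol say that baseline-only patients count as zero change.
- **That the comparison will reverse.** None of the scenarios restricted to true withdrawals reverses the assumed +12 benefit. Reversal needs early, clearly unequal loss of questionnaires, and in the example above it also needs baseline values carried forward.
- **That the standard errors are too small.** For the planned t-test this is not borne out. In 4,000 simulated trials with equal 3-month median retention, the mean standard error and the empirical standard deviation of the difference were both about 4.1, and the type I error was close to 5%. The fault is bias.

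**Conclusion.** The concern holds in limited form. LOCF with an undefined qualifier is the only stated rule for withdrawn participants, it lands on the questionnaire scores, and it is unsuited to scores that decline. Equal withdrawal attenuates a true difference. Unequal withdrawal can also produce a spurious one, or inflate a real one if BJOEI patients leave faster.

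The illustrative size is about -4.2 points against BJOEI when the truth is 0, and +7.0 in place of +12, at 10% versus 30% withdrawn by month 6. Slopes, withdrawal rates, the month-6 time point and the treatment of baseline-only patients are all assumptions; leaving baseline-only patients out gives -2.2 and +9.4. The primary PFS analysis is unaffected. The plan should be changed, because the remedy is cheap and the results are meant to inform phase III.

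**What to change.** Delete the LOCF sentence and replace it with the following.

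1. Analyse the QLQ-C30 and symptom scores with a likelihood-based repeated-measures model containing baseline score, arm, visit, arm-by-visit interaction and the minimisation factors. Use every score observed while the patient is alive, and impute nothing after death.
2. Add one sensitivity analysis for informative dropout or death, for example time to deterioration with death counted as an event.
3. State that PFS and OS use censoring only.

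The cost is a change of wording and slightly more analysis work; no new data are needed. The model assumes that scores are missing at random while patients are alive, which is why the sensitivity analysis belongs with it.

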#### Analysis populations

We have clearly pre-defined the analysis populations as follows:(1) The modified intention-to-treat (mITT) population will include all randomized patients who receive at least one dose of study treatment (Brucea javanica Oil Emulsion Injection or best supportive care).(2) The per-protocol (PP) population will comprise patients in the mITT population who complete the study without major protocol deviations, specifically defined as patients who receive ≥80% of planned treatment doses, have no prohibited concomitant medications, and complete all required safety and efficacy assessments per protocol schedule.(3) The safety set will include all patients who receive at least one dose of study treatment and have at least one post-baseline safety assessment.

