#### Safety outcomes

We will adopt a more rigorous daily monitoring regime throughout the 14-day infusion cycles, incorporating vital signs monitoring, comprehensive clinical symptom assessment, and laboratory test. This enhanced monitoring approach will enable immediate detection and management of infusion-related adverse events, thereby improving patient safety during the most critical treatment periods. Any AEs that arise will be promptly documented, and the physician will provide treatment based on the specific circumstances. Serious AEs will be reported to the ethics committee. Insurance will cover any AEs resulting from the study.

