#### Primary and secondary analyses

The primary efficacy analysis will be conducted on the mITT population, with supportive analyses performed on the PP population. Safety evaluations will utilize the safety set. The primary endpoint analysis will focus on PFS, while secondary endpoints will include response rate, OS, quality of life measures, and safety parameters.

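### Safety-set entry needs a post-baseline assessment that BJOEI patients get almost at once and controls may get late; separately, unequal monitoring makes crude AE frequencies non-comparable

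*Protocol article*

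**What the plan says.** The protocol article, under Analysis populations, defines the set: "The safety set will include all patients who receive at least one dose of study treatment and have at least one post-baseline safety assessment". Under Primary and secondary analyses it adds: "Safety evaluations will utilize the safety set". The mITT set, used for efficacy, requires only a first dose, with BJOEI and BSC both named as study treatment. What a dose of BSC means is not said.

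Under Safety outcomes: "We will adopt a more rigorous daily monitoring regime throughout the 14-day infusion cycles". This covers vital signs, symptoms and laboratory tests, and its stated aim is "immediate detection and management of infusion-related adverse events". Under Study design the experimental arm receives "30 mL of intravenous BJOEI daily for 1–14 days in each 28-day cycle", and then: "Conversely, the control group will receive only BSC".

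The one visit interval in the readable text is also under Study design: "Follow-up evaluations will occur every 2 months until either death, loss of follow-up, or the 12-month mark from randomization". It is not specific to either arm. The Safety outcomes section also says that AEs are recorded promptly as they occur and that serious AEs go to the ethics committee, again without restriction to one arm.

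**The concern.** Two separate problems arise, from two different places in the article.

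**Who enters the safety set.** Entry depends on something that happens after randomisation, and the opportunity for it differs by arm. An infused patient can meet the condition on the first treatment day. No comparably early safety contact is stated for a control. The patients have stage IV disease refractory to all available therapy with ECOG status up to 2, so some early deaths are to be expected. If a control dies or is lost before any assessment, the rule as worded can remove that patient from the safety tables. This would take fatal and serious events out of the control column.

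**What is detected among those who enter.** This follows from the monitoring regime, not from the set definition. Symptoms and laboratory values are looked for daily in one arm during infusion periods, and no matching regime is stated for the other. With equal true event rates, more minor and laboratory AEs would be recorded on BJOEI.

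The study is described as comparing efficacy and safety between arms, and its stated purpose is to inform a phase III trial. A safety contrast shaped by who was looked at, and how often, would be a poor input to that trial.

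**Working it through.** **The plan's own figures.** There is no safety figure to reproduce. The sample size is 30 + 30 = 60, chosen as a pilot size, with no death rate or AE rate given. The calculations below only show what the rule could do. All survival and event rates in them are assumptions.

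**Inputs from the article.** 30 patients per arm (Sample size); daily monitoring in the 14-day infusion periods (Safety outcomes); infusion schedule, read here as days 1 to 14 of 28 (Study design); 2-monthly follow-up (Study design).

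**Inputs assumed.** Exponential survival with a median OS of *m* = 4 to 9 months; first control safety assessment at *t* = 2 months or 1 month; a death does not itself count as an assessment.

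**Step 1: deaths before the first assessment.** P = 1 − exp(−ln 2 × t / m), and the expected number is 30 × P.

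| Assumed median OS (months) | First assessment at 2 months | First assessment at 1 month |
|---|---|---|
| 4 | 0.293 → 8.8 of 30 | 0.159 → 4.8 of 30 |
| 5 | 0.242 → 7.3 | 0.129 → 3.9 |
| 6 | 0.206 → 6.2 | 0.109 → 3.3 |
| 7 | 0.180 → 5.4 | 0.094 → 2.8 |
| 9 | 0.143 → 4.3 | 0.074 → 2.2 |

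For example, with m = 6 and t = 2: 1 − exp(−0.693 × 2/6) = 0.206, and 30 × 0.206 = 6.2. With a 2-month first assessment, the chance of at least one such control death is 1 − (1 − P)^30, which is 0.99 even at a 9-month median.

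For BJOEI with a day-1 assessment (t = 1/30.4 month), the same formula gives 0.1 to 0.2 of 30.

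**Step 2: effect on a control safety table.** Take m = 6 and a 2-month first assessment. Mortality by 6 months in all controls is 0.500. Among those still in the set it is (0.500 − 0.206) / (1 − 0.206) = 0.37.

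**Step 3: if deaths or AE reports count as assessments.** A control who dies or has a reported event then qualifies, and the number dropped because of early death falls to near zero.

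**Step 4: detection.** Assume the same AE rate of 0.3 per month in both arms, AEs lasting 7 days, a 56-day window, 28 daily-watched days on BJOEI, one look at day 56 for controls, and no recall or spontaneous reporting.
- BJOEI: 1 − exp(−0.3/30.4 × (28 + 7)) = 0.29
- Control: 1 − exp(−0.3/30.4 × 7) = 0.07

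At this rate, with AEs lasting 3 days the figures are 0.26 and 0.03; with 14 days they are 0.34 and 0.13. This is an extreme case: recall at visits and unscheduled reports would narrow the gap. It shows the direction and does not estimate the size.

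**The case against.** The strongest reply is that the control schedule is unknown, not absent. The participant timeline figure is not shown. The per-protocol definition refers to a schedule of required safety and efficacy assessments, and the Discussion mentions regular haematology and chemistry monitoring without limiting it to one arm. A condensed article would normally leave a visit calendar to the full protocol. This stands. A reader might infer that controls are checked for safety only every 2 months, and hence that assessment frequency differs about 30-fold (14 per 28 days against 28/60 = 0.47). The documents do not support that: the 2-monthly interval is a general follow-up interval for both arms, and the ratio counts presumed visits, not detected events.

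A reader might also infer that early control deaths are certain to drop out. That needs a death or AE report not to count as an assessment, and the article says neither that it does nor that it does not. Since AEs and serious AEs are to be recorded as they occur, some such controls may qualify. Their deaths also stay in PFS and OS, because the mITT set has no assessment condition. These points limit the harm to the safety tables.

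It can further be said that closer watching of an infused arm is natural in an open-label comparison with BSC, that the rule for chi-squared or Fisher tests is generic and no AE test is named, and that the trial is an unpowered pilot. All true. Even so, a descriptive table of AE percentages by arm would carry the same distortion.

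Finally, simply removing the condition would bring in controls with no safety data, who could be read as free of AEs. That is a fair warning, and the fix has to deal with it.

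**Conclusion.** The point holds in limited form. The text itself fixes three things: entry to the safety set depends on an assessment after baseline, all safety evaluations use that set, and intensive monitoring is tied to infusions that only one arm receives. It leaves open whether a death or a spontaneous AE report satisfies the condition, and what a dose of BSC is. Control membership is therefore ambiguous on both criteria.

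The number of controls affected cannot be known from the article. The illustrative range runs from near zero (deaths count) through 2.2 to 4.8 of 30 (first assessment at 1 month) to 4.3 to 8.8 of 30 (at 2 months). It rests on assumed exponential survival and an assumed first assessment date. The detection problem is independent of this and would remain if only the set definition were reworded. Crude between-arm frequencies of low-grade and laboratory AEs should not be read as a drug effect. Neither problem touches the primary PFS analysis. Both are worth correcting because they are avoidable at little cost.

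**What to change.** 1. Define the safety set as all patients given any BJOEI plus all randomised patients not given BJOEI, with no condition on a later assessment. This also removes the undefined dose of BSC from the criterion.
2. State that every death and every reported AE counts as safety information, whether or not it arose at a scheduled visit.
3. Report by arm how many patients had no safety follow-up, and give exposure-adjusted rates, so that patients without data are not taken as event-free.
4. Limit between-arm comparison to deaths, serious AEs, grade 3 or higher events, and findings at visits common to both arms.
5. Tabulate findings from infusion-day monitoring descriptively, for BJOEI only.

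Items 1 and 2 address entry to the set, item 3 deals with patients who have no data, and items 4 and 5 address unequal detection. The cost is a change of wording and some extra tables, with no change to patient care. The downside is that fewer low-grade events enter the comparative table.
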